### Usual physiotherapy care

2.6

All participants will receive physiotherapy care as usual. The details of usual care received by participants will be recorded. To do this, participants will indicate their co-interventions by selecting from a list of possible types: manual therapy, exercise interventions, home-based exercises, coaching, education, cognitive interventions, pharmacological interventions, invasive interventions, and interventions using applications.

### Experimental group

2.7

Participants allocated to the experimental group will undergo four weeks of in-home tactile acuity training with the iTAD in addition to their usual physiotherapy care. The iTAD consists of a wearable neoprene collar, containing 12 hemispherical nodes, each enclosing a vibrotactile stimulator (see Fig. 2; a full description has been published previously [17]. The nodes contact the back of the neck and are wirelessly connected to tablet computer with a custom-written software application. The application triggers vibrotactile stimulations, records the user responses, provides feedback and calculates accuracy scores. Training consists of two types of (serious) games: The *localisation game*, where users indicate the location of a single vibration by selecting the corresponding location on the tablet; and the *orientation game*, where users indicate the direction of a second vibration, relative to a first, by selecting the corresponding arrow. The explanation given to participants relating to how iTAD may improve symptoms is standardised (See Appendix 1).

**Fig. 2 fig2:**
[figure not shown]
The Imprint Tactile Acuity Device (iTAD) and wirelessly connected tablet displaying the localisation (top right) and orientation (bottom right) applications.

### Control group

2.8

Participants in the control group will undergo their usual physiotherapy care plus a placebo intervention. The placebo component of the control intervention is specifically designed to control for non-specific effects of the iTAD. The participants in the control group will undergo four weeks of in-home use of a placebo Transcutaneous Electrical Nerve Stimulation (TENS) unit that will be referred to as iTENS (inhibitory TENS). In order to match time spent with the iTAD, participants will be instructed to use the iTENS for 1 h per day, five days per week. The iTENS devices are altered such that no electrical current is delivered to the user. However, the unit will look fully operational (Fig. 3). The explanation given to participants relating to how iTENS may improve symptoms is standardised (See Appendix 1).

**Fig. 3 fig3:**
[figure not shown]
The iTENS machines used to deliver the placebo control intervention, showing the unit, wires and adhesive pads.

### Treatment fidelity and progression

2.9

In order to aid adherence and ensure fidelity to protocol, participants will be contacted by the study clinician on a weekly basis during the 4-week intervention and participants will attend a mid-treatment outcome assessment in person. In the experimental group treatment is progressed automatically by increasing the difficulty of the tactile acuity games, the mid-treatment review will be used to implement a false progression of the placebo iTENS machine. Participants will also maintain a treatment log to record frequency and duration of treatment sessions. In the intervention group this will be cross-referenced to the iTAD software usage data for verification.

### Primary outcome measures

2.10

Tactile acuity measures will be assessed prior to the intervention (baseline), and at mid-treatment, 5-week follow-up (i.e., within 1-week of treatment completion and 5-weeks after commencement), and 2-month follow-up (i.e., 2-months after commencement) (See Table 1). Data relating to feasibility will be collected throughout the study.

**Table 1 tbl1:** Outcomes measures.

	Domain	Measures	Timepoints
Primary outcomes	Tactile acuity	Two-point discrimination Locognosia	1,2,3,4
			1,2,3,4
	Feasibility	Recruitment rates, adherence (training duration), dropouts Bang's Blinding Index Perceived treatment credibility (Credibility Scale)	Throughout
			4
			*1
Secondary outcomes	Pain Intensity	Pain intensity: 0–10 NRS current, average & worst pain in the past week	1,2,3,4
	Pain spread	Self-indicted on body chart	1,2,3,4
	Tactile acuity	iTAD overall score	1,2,3,4
Exploratory outcomes	Perceived change	Global Perceived Effect (GPE)	2,3,4
	Disability	Neck Disability Index	1,2,3,4
	Tactile acuity	iTAD sub-scores	1,2,3,4
Exploratory predictors	Training hours	Training log	4
	Sleep	Insomnia Severity Index	3
	Psychological	Depression Anxiety & Stress Scale	1
	Baseline measures	Tactile acuity	1

*Time points: 1 = baseline, *1 = three days into the intervention, 2 = mid-treatment, 3 = 5-week outcome assessment (within 1-week of intervention completion), 4 = 2-month outcome assessment.

***Two-point discrimination threshold:*** The participant will be seated with their head resting on their hands on a table in front of them, and a digital sliding two-point Vernier Calliper will be placed under its own weight on the participant's skin to provide two simultaneous tactile stimuli. The calliper will be aligned in a cranio-caudal direction, with the most caudal arm 15 mm lateral to the spinous processes of C7 on the most painful side of the neck. Should pain be bilateral and equal, the side of their dominant hand will be tested. Assessment will commence with the two-points at a 20 mm separation and will be increased by 5 mm increments until the participant report feeling two points of contact. When two distinct points are perceived in three consecutive trials this value will be recorded. The calliper distance will then be increased by a further 10 mm and the same procedure will be performed in reverse, with all following assessments in steps of 2 mm. A series of three ascending and descending assessments will be performed, with the mean of the six values used for analyses. TPDT has excellent intra-rater reliability at the neck (ICC = 0.85, SEM 3.7 mm) [21].

***Locognosia:*** Locognosia, the ability to localise touch, will be assessed with a manual localisation task. Twelve locations (numbered 1–12) will be marked on the neck, in three rows of four, matching the number and inter-node distances (32.5 mm apart in both the vertical and horizontal) of the iTAD. Using the back of the SENSELab brush-05, pressure will be applied to each location three times in a block semi-randomised order. Each block contains one stimulus per location, alternating sides of the neck. Participants will look at a photo of their own neck, with the locations marked, on a tablet and report the number of the location they think is touched. A percentage correct score will be calculated to quantify localisation accuracy. A similar manual locognosia test has demonstrated good (ICC_2.1_ = 0.86) to excellent (ICC_2.1_ = 0.92) intra-rater reliability [33] as well as construct validity using a known-group comparison [33].

***Feasibility:*** Feasibility, with respect to planning a full-scale RCT, will be assessed according to recommended a framework [34]. Data to assess feasibility will be extracted from a digital record of recruitment and screening-related interactions, iTAD digital usage logs, participant completion rates, and questionnaires related to blinding, treatment credibility, and treatment satisfaction. For the protocol to be classified as feasible, a priori cut offs have been determined. These include: 1. A minimum intake of two participants per week and a positive recruitment rate of at least one participant intake out of every four invited, 2. An 80% treatment completion rate, 3. A follow-up rate of 70%, 4. A maximum of 10% missing data for primary and secondary outcomes for those that completed the study, 5. Adherence rates where at least two-thirds of participants complete over 50% of the prescribed training, 6. No statistically significant difference in credibility between intervention and control, a 7. Bangs blinding index of 0 ± 0.2 for both treatment arms as well as the outcome assessor (on a −1 to 1 scale, where scores closer to 0 represents being more unsure of group) [[35], [36], [37]], and 8. Neutral positive satisfaction with treatment ratings for both treatment arms.

***Adverse events:*** For the purpose of this trial, a serious adverse event is defined as an unwanted and harmful outcome that: 1. be related to the intervention, and 2. is significant enough to require medical attention. A minor adverse event will be defined as any unwanted outcome that: 1. either interferes with activities of daily living or persists for more for 24 h, and 2. can be related to the intervention. Adverse events will be monitored during the weekly phone calls with the study clinician.

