### Blinding

2.4

A limited deception approach will be used to maintain participant blinding. While participants understand they will be randomised to one of two groups, one of which may be usual care plus a placebo, once the intervention phase commences the therapist will act as though participants are undergoing active interventions regardless of allocation. Additionally, participants will be blinded towards the allocation ratio. The researcher responsible for assessing outcomes will also be blind to group allocation. A questionnaire with five response categories will be used to quantify blinding of the patient and outcome assessor at the end of the study [26]. Bang's blinding index will be calculated for each treatment arm, as well as for the outcome assessor to estimate blinding success [26]. Patients will also be asked to complete the Credibility Scale to establish the degree to which the iTAD and iTENS interventions were perceived as legitimate [27]. The Credibility Scale will be completed verbally over the phone three days into the intervention.

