### Sample size

2.5

Previous single-armed trials investigating (manual) tactile training for patients with chronic pain found moderate to large effect sizes for within group change in tactile acuity (26% improvement, mean change: TPDT 17.1 mm, p < 0.01, Cohen's d = 1.06) [28] and pain intensity (22% improvement, mean change: VAS 1.0 cm, p = 0.02, Cohen's d = 0.55) [16]. We therefore expect that we need to reach at least medium-large effects in tactile acuity in order to mediate clinically meaningful changes in pain. However, these effect sizes are based on within-group change since a control group was not present. Nevertheless, similar size differences in change of pain intensity have been reported when comparing tactile acuity training to a control condition for: neck pain [29] (24% difference, Δ NRS 1.6 points, p = 0.02, Cohen's d = 0.44); back pain [29] (41% difference, mean change: NRS 2.3 points, p < 0.01, Cohen's d = 1.07); and phantom limb pain [30] (45% improvement, mean change: Multidimensional Pain Inventory 1.5 points, p = 0.02, Cohen's d = 1.16). However, since these studies did not include tactile acuity as an outcome measure, they are not directly informative for our primary research question. As such, a sample size calculation was performed to account for a >90% chance of finding a statistically significant (p < 0.05), medium-large ($\eta_{p}^{2}$ = 0.1) between-group difference in tactile acuity, using a within-between repeated-measures ANOVA with four time-points. The calculation estimated that 18 participants would be required. Accounting for a dropout rate which can be up to 20% for treatments involving active participation in people with health conditions [31,32] a pool of 24 participants (12 in each arm) were estimated to be necessary. To improve power to explore secondary outcomes, particularly within the tactile training group, the target sample size for the intervention arm was doubled (n = 24 intervention group; n = 12 control group).

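### Feasibility criterion 6 is passed by a non-significant credibility test, so at 24 vs 12 a moderately less credible placebo passes more often than it fails

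*Protocol article*

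**What the plan says.** Section 2.10 (Primary outcome measures, Feasibility paragraph) introduces eight pass marks: "For the protocol to be classified as feasible, a priori cut offs have been determined". The sixth is "No statistically significant difference in credibility between intervention and control". No margin, confidence interval, minimum credibility score or power is given for this comparison.

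Section 2.4 (Blinding) gives the purpose of the Credibility Scale: "to establish the degree to which the iTAD and iTENS interventions were perceived as legitimate". It is completed once, by phone, three days into the intervention. Table 1 places it under the primary feasibility outcomes.

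Section 2.5 (Sample size) fixes the arm sizes: "the target sample size for the intervention arm was doubled (n = 24 intervention group; n = 12 control group". The only power calculation there is for tactile acuity.

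**The concern.** A test that does not reject can mean that the arms are similar, or that the sample is too small to tell. Criterion 6 counts both as a pass, and fewer completed questionnaires make passing easier. Section 2.4 sets an estimation aim, namely how legitimate each intervention appears. A significant/non-significant verdict does not serve that aim.

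Section 2.8 says that the placebo is there to control for the non-specific effects of iTAD. The comparison sets an interactive, game-based training device against a unit that delivers no current, so unequal credibility is a realistic possibility. If iTENS is materially less believable, differences in acuity and pain could partly reflect expectation. A pass on criterion 6 could then help to carry a weak control into the full-scale trial that these feasibility results are meant to inform.

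**Working it through.** **The plan's own figure.** Section 2.5 describes "a sample size calculation was performed to account for a >90% chance of finding a statistically significant" medium-large effect (partial eta squared 0.1), for a "between-group difference in tactile acuity, using a within-between repeated-measures ANOVA with four time-points". It then reports: "The calculation estimated that 18 participants would be required". Read as the group-by-time interaction:

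- f² = 0.1/0.9 = 0.111, so f = 0.333.
- λ = f² × N × 4/(1 − ρ), with df 3 and 3(N − 2). The correlation ρ = 0.5 and sphericity are assumed, because neither is stated.
- N = 18 gives power 0.912 and N = 16 gives 0.869, so 18 is reproduced.
- Dropout of 20%: 9/0.8 = 11.25 per arm, rounded up to 12, or 24 in total. Doubling the intervention arm gives 24 vs 12.

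This figure is consistent for tactile acuity. It says nothing about the power of the credibility comparison.

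**Inputs for criterion 6.** Arm sizes 24 and 12 (section 2.5). Assumed: one credibility score per person, a two-sided t-test at 5% (section 2.5 states 0.05 for acuity only) and equal SDs. Deficits d are in SD units.

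**Largest observed gap that still passes.**

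- SE = √(1/24 + 1/12) = √0.125 = 0.354 SD.
- Critical value t(0.975, 34 df) ≈ 2.03.
- 2.03 × 0.354 = 0.72 SD, which is also the half-width of the 95% CI.

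**Chance of passing now.** Noncentral t with 34 df and noncentrality d × √(24 × 12/36) = d × √8. The chance of passing is one minus the power.

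**Chance of passing under a point-estimate rule.** With an illustrative margin of 0.5 SD, the chance is Φ((0.5 − d)/0.354).

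| True iTENS deficit | Passes now | Passes with 0.5 SD margin |
|---|---|---|
| 0 | 95% | Φ(1.41) = 92% |
| 0.5 SD | 72% | Φ(0) = 50% |
| 0.7 SD | 51% | Φ(−0.57) = 29% |
| 0.8 SD | 41% | Φ(−0.85) = 20% |
| 1.0 SD | 21% | Φ(−1.41) = 8% |

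Under the current rule the chance of passing falls to one half at 0.71 SD. Power reaches 80% only at 1.02 SD. Detecting 0.5 SD with 80% power at 2:1 allocation would need about 144 participants.

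**Sensitivity.** A simulated Mann-Whitney test at 24 vs 12 passes 0.5 SD 73% of the time and 0.8 SD 43%, so the result does not hinge on the t-test. With three respondents missing (22 vs 11) the t-test figures are 74% and about 45%.

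**What a demonstration of similarity would require.** If the one-sided 95% confidence bound had to lie inside the margin, a truly equal placebo would pass 40% of the time at 0.5 SD, 72% at 0.8 SD and 87% at 1.0 SD. Thirty-six participants cannot support a tight margin on that basis.

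**The case against.** - **Size of the deficit.** A reader might infer that any clearly less credible placebo would usually pass. The figures do not support that. Passing is the likelier result only up to about 0.71 SD; at 0.8 SD the placebo fails more often than it passes, and at 1.0 SD it passes 21% of the time.
- **No claim of equality.** The protocol does not say that non-significance proves equal credibility. It uses it as a pass mark in a proof-of-concept trial. That stands, but the pass mark still has the weakness described.
- **Other safeguards.** Criterion 6 is one of eight. Criterion 7 requires a Bang index within 0 ± 0.2 for each arm and the assessor, and criterion 8 sets a satisfaction rule for both arms. An unconvincing placebo might show up there, so the percentages above apply to criterion 6 alone and not to the overall feasibility verdict. However, neither criterion bounds the credibility difference: the Bang index concerns guessed allocation at the final assessment, and satisfaction is judged within each arm.
- **Reporting.** Section 2.13 allows for effect sizes and descriptive statistics where appropriate, so planners of the next trial may see more than a p-value. This does not alter the pass rule.
- **Missing questionnaires.** It is tempting to apply the 20% dropout allowance and claim a much worse result. Credibility is collected by phone on day three, and criterion 4 caps missing data at 10% among completers, so heavy loss is not well grounded. The case rests on 24 vs 12.
- **The remedy.** A point-estimate rule passes a deficit exactly at its margin half the time, and the documents provide no basis for 0.5 SD. Both points stand.

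**Conclusion.** The point holds for moderate deficits. Criterion 6 is a stated decision rule, not a detail left to an analysis plan, and it is the only one of the eight cut-offs that is passed by a non-significant test. At 24 vs 12 an iTENS deficit of 0.5 to 0.7 SD passes 72% to 51% of the time, and a large one of 0.8 SD passes about two times in five. These figures assume a two-sided 5% test on one score with equal SDs; the documents state neither the test nor the SD. It would go too far to conclude that a poor control would probably be declared feasible overall, since the other cut-offs must also be met and their joint behaviour cannot be calculated from the document. The change is worth making, and it does not affect the tactile acuity sample size.

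**What to change.** Replace criterion 6 with a cut-off on size, in line with the other numeric criteria. For example: *the observed mean iTENS credibility score is no more than [X] scale points below the iTAD mean; the difference is reported with its 95% confidence interval, and no significance test is used. With 36 participants this is a screening rule and does not demonstrate equivalence.*

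The sponsor should choose and justify X before the data are seen; the 0.5 SD used above only illustrates how such a rule behaves.

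The cost is one sentence in the protocol and the need to settle a margin. The criterion becomes slightly harder to meet when credibility is truly equal (92% against 95% at 0.5 SD), and a deficit exactly at the margin still passes half the time. The rule as worded looks in one direction only. If iTENS being more credible than iTAD should also count as a failure, the margin can be applied on both sides; at 0.5 SD an equal placebo would then pass about 84% of the time (1 − 2 × 0.079).

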**Methods:**

and analysis: In this two-arm randomised clinical proof-of-concept trial we will recruit participants with neck pain receiving usual care physiotherapy in a secondary outpatient healthcare setting. Thirty-six participants will be randomised 2:1 to receive four weeks of either tactile acuity training using the Imprint Tactile Acuity Device (iTAD) or a placebo intervention, in addition to usual care. The placebo intervention will consist of a de-activated TENS machine (iTENS) said to deliver a sub-threshold inhibitory therapy. Outcomes will be assessed at baseline, mid-treatment, and at 5-weeks and 2-months follow-up. The primary outcome tactile acuity will be evaluated using the two-point discrimination test and locognosia tests. Feasibility will be informed by recruitment and attrition rates, adherence, credibility of the interventions, treatment satisfaction and blinding. Pain intensity and anatomical spread will be analysed as secondary outcomes. The effect of iTAD training on tactile acuity will be assessed using a 2 (Group: iTAD vs. iTENS) x 4 (Time: baseline, mid-treatment, 5-week and 2-month outcome assessment) mixed ANOVA. Secondary outcomes including pain and pain spread, will be analysed with a focus on informing sample size calculations in future trials.

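### Feasibility criterion 7 (Bang index within 0 ± 0.2 in each arm) would score a convincing placebo as failed blinding, and the window is narrow for arms of 24 and 12

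*Protocol article*

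**What the plan says.** Table 1 and section 2.10 of the protocol article make feasibility a primary outcome domain. The feasibility paragraph says "For the protocol to be classified as feasible, a priori cut offs have been determined" and lists eight. The seventh is a "Bangs blinding index of 0 ± 0.2 for both treatment arms as well as the outcome assessor", with the index described as "on a −1 to 1 scale, where scores closer to 0 represents being more unsure of group".

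Section 2.4 (Blinding) gives the measurement: "A questionnaire with five response categories will be used to quantify blinding of the patient and outcome assessor at the end of the study", and "Bang's blinding index will be calculated for each treatment arm, as well as for the outcome assessor to estimate blinding success". It does not give the scoring weights for the five categories, or say whether the assessor's index is pooled or taken by arm.

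The same section describes the deception: "the therapist will act as though participants are undergoing active interventions regardless of allocation". It adds that "participants will be blinded towards the allocation ratio" and does not say whether the assessor knows the ratio. Sections 2.8, 2.9 and 2.15 support the deception with a TENS unit that appears to work, a staged progression at mid-treatment, and explanations revised with patients so that the control is believed. On size, the abstract says "Thirty-six participants will be randomised 2:1", and section 2.5 gives 24 iTAD and 12 iTENS participants.

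**The concern.** Bang's index is computed within an arm as correct minus incorrect guesses. In the iTAD arm, believing in active treatment is a correct guess. In the iTENS arm, the same belief is an incorrect one. A placebo that convinces people therefore pushes the iTENS index below zero while the iTAD index rises above it. Criterion 7 sets the same window around zero in each arm, so it treats this pattern like unblinding. Criterion 6 in the same list asks that the two interventions be equally credible; if both are equally and highly credible, criterion 6 is met and criterion 7 fails.

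The list decides whether the protocol is suitable for a full-scale trial. A failure on criterion 7 could be read as a defect of the control condition when the control did what it was designed to do.

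**Working it through.** **Inputs.** Window ±0.2 for each index (section 2.10). Arm sizes 24 and 12 (section 2.5). Dropout up to 20% (section 2.5) and a follow-up cut-off of 70% (section 2.10). Response probabilities and scoring weights are not in the article. I assume three-way scoring (+1, 0, −1) or five-category scoring (+1, +0.5, 0, −0.5, −1) and show a range.

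**The plan's own figure.** The article gives no pass probability for criterion 7. The sample size behind the arms does reproduce: N = 18 gives power 0.912 for the interaction (partial eta squared 0.1, four time points, assuming correlation 0.5 and sphericity). Then 18/(1 − 0.2) = 22.5, so 23, or 24 as an even number. Doubling the intervention arm gives 24 + 12. This is not in dispute.

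**Step 1: what the index measures.** Let b be the share answering active minus the share answering placebo. Then BI(iTAD) = b(iTAD) and BI(iTENS) = −b(iTENS). The mean of the two is [b(iTAD) − b(iTENS)]/2, half the between-arm difference in belief. It is zero whenever belief does not depend on arm, whatever its level. The separate indices are both near zero only if b is near zero in both arms.

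**Step 2: the deception works equally in both arms.** Assume 60% active, 20% unsure, 20% placebo in each arm. BI(iTAD) = 0.60 − 0.20 = +0.4; BI(iTENS) = 0.20 − 0.60 = −0.4. The window allows a net of at most 4 guesses out of 24 (0.2 × 24 = 4.8) and 2 out of 12 (0.2 × 12 = 2.4). The exact distribution, by convolving the response probabilities, gives P(pass) = 0.100 for iTAD and 0.195 for iTENS, so 0.100 × 0.195 = 0.0195 for both. Milder shared belief (40/40/20, indices ±0.2) passes in 22%.

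**Step 3: pure guessing, no belief either way.** Exact pass probabilities at 24 and 12:

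| Response mix | iTAD | iTENS | Both arms |
|---|---|---|---|
| Three-way, 0% unsure | 0.69 | 0.61 | 0.42 |
| Three-way, 20% unsure | 0.69 | 0.58 | 0.40 |
| Three-way, 50% unsure | 0.81 | 0.69 | 0.56 |
| Three-way, 70% unsure | 0.91 | 0.82 | 0.74 |
| Five-way, all equally likely | 0.83 | 0.64 | 0.53 |

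For the last row the variance per answer is (1 + 0.25 + 0 + 0.25 + 1)/5 = 0.5, so the SE is √(0.5/12) = 0.204 for iTENS and √(0.5/24) = 0.144 for iTAD. At 70% follow-up (about 17 and 8 answering), the three-way rows run from 0.18 to 0.60 for both arms.

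**Step 4: the assessor.** An assessor with no information who always answers iTAD scores (24 − 12)/36 = +0.33 if pooled, or +1 and −1 by arm; both readings fail. An assessor who answers iTAD two-thirds of the time has an expected pooled index of 2/3 × 1/3 − 1/3 × 1/3 = +0.11, which passes in 67%, or +0.33 and −0.33 by arm, which passes in 9%.

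**Step 5: alternatives for participants.** Same exact method. The combined rule passes if the absolute mean of the arm indices is at most 0.2 and BI(iTENS) is at most +0.2.

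| Scenario (iTAD / iTENS index) | Current rule | Mean only | Combined |
|---|---|---|---|
| Shared belief, +0.4 / −0.4 | 2% | 84% | 84% |
| Unblinded, +0.4 / +0.4 | 2% | 8% | 7% |
| Unblinded, +0.3 / +0.3 | 8% | 24% | 20% |
| Controls detect device, 0 / +0.4 | 13–14% | 48% | 19% |
| Belief higher under iTAD, +0.4 / 0 | 6% | 49% | 48% |
| Guessing, 0% to 70% unsure | 40–74% | 71–96% | 62–89% |

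All rows use three-way scoring, with 20% unsure in the first five.

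**The case against.** The best defence is that the target is deliberate. Participants are told that one group may receive a placebo, section 2.10 states the goal as uncertainty about group, and it cites sources that are not to hand. The 60/20/20 split is also an assumption with no figure behind it in the article. The second part stands, which is why the 2% is tied to that split. The first does not rescue the rule: sections 2.4, 2.8, 2.9 and 2.15 work towards belief in both arms, not indifference, and even mild shared belief passes in only 22%.

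A reader might infer three stronger conclusions that the documents do not support.

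- *That perfect blinding fails half the time by chance.* The article gives neither response mix nor weights. Two-arm failure runs from about 60% down to about 26% when 70% are unsure, and lower still if more are. The completion, follow-up and adherence cut-offs also carry sampling error in a trial of 36.
- *That the assessor will fail.* Step 4 needs an assessor who knows or infers the ratio and always names the larger arm. The article is silent on that knowledge and on pooling.
- *That the mean of the two indices can simply replace the rule.* Alone, it passes a trial in which controls detect the inert device in 48% of cases, against about 13% now.

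It is also fair that the index is already planned by arm, so a plus/minus pattern would be visible, and that section 4 ties further development to tactile acuity and pain rather than to blinding.

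**Conclusion.** Criterion 7 is wrong as written because it conflicts with the blinding strategy it is meant to judge. This is structural: a larger sample would make a convincing placebo fail more surely. The size, about 2% passing, rests on equal belief of 60/20/20, three-way scoring, independent arms and full follow-up. The narrowness of the window is a secondary point, best stated as a range: about 40% to 74% of trials pass on both arms under pure guessing with 0% to 70% unsure. The assessor point is conditional on knowledge of the ratio.

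Severity is moderate. One of eight feasibility cut-offs can give the wrong answer, but the tactile acuity analysis and the sample size are untouched. A reader might take the point as casting doubt on the efficacy comparison; nothing in the documents supports that.

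**What to change.** Reword criterion 7 before the end-of-study blinding questionnaires are analysed:

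1. A positive iTAD index paired with a negative iTENS index of similar size is read as shared belief in active treatment, not as unblinding.
2. Unblinding of participants is flagged if the mean of the two arm indices lies beyond ±0.2, or if the iTENS index exceeds +0.2, so that controls who detect the inert device are not cancelled out.
3. The assessor's index is computed by arm and its mean judged in the same way. An assessor who always names the larger arm then scores (+1 − 1)/2 = 0.
4. Every arm-specific index is reported with its 95% CI, the scoring weights are stated, and the cut-off serves as guidance given the small arms.

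The cost is wording only; no new data are needed. The drawback is lower sensitivity to moderate or one-sided patterns. On the mean alone, 0/+0.4 passes in about 48% of trials and +0.3 in both arms in about 24%. The iTENS condition brings the first down to about 19%, but +0.4/0 still passes in about 48%. The arm-specific indices must therefore remain part of the decision.

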### Strengths and weaknesses of the study

3.2

A strength of the study is the use of participants attending secondary care, a population that may be more likely to present with a significant central nervous system adaptation as a contributor to their symptoms. Further, we have implemented tools to assist in controlling for non-specific effects and bias such as a placebo intervention and blinded assessors. Weaknesses of the study include its inability to blind the therapist and inability to draw conclusions on secondary outcomes due to the low participant numbers in this proof-of-concept study. However, results relating to secondary and exploratory outcomes will assist to inform larger scale studies aiming to determine whether tactile training can improve outcomes such as pain.

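### Both adverse event definitions require relatedness to the intervention, and the only stated collection ends with the 4-week calls, about halfway through follow-up

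*Protocol article*

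**What the plan says.** The protocol article defines two categories of adverse event in section 2.10.

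- **Serious:** "a serious adverse event is defined as an unwanted and harmful outcome that: 1. be related to the intervention", and that is bad enough to need medical attention.
- **Minor:** an unwanted outcome that disturbs daily activities or lasts beyond a day, and that "2. can be related to the intervention".

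In each category both conditions must hold. On collection, the same paragraph says: "Adverse events will be monitored during the weekly phone calls with the study clinician". Section 2.9 gives the period of those calls: "participants will be contacted by the study clinician on a weekly basis during the 4-week intervention". Participants remain in the study after the calls stop, with an assessment at 5 weeks and a final one at the "2-month follow-up (i.e., 2-months after commencement").

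On blinding, section 2.4 says: "The researcher responsible for assessing outcomes will also be blind to group allocation". Section 3.2 concedes the "inability to blind the therapist". Section 2.8 says that the control unit is altered so that it passes no current. Adverse events do not appear in Table 1, in the eight feasibility cut-offs or in the data analysis section.

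**The concern.** Whether an event happened, how serious it was and what caused it are three separate questions. Here the answer to the third decides whether the event counts at all. Once that filter is applied when the event is reported, nobody can later compare all events between arms or revisit a causality call, because the filtered events have no category to sit in.

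The filter may also act differently in the two arms. Someone who knows that the control unit is inactive has a reason to call a control-arm event unrelated. That reason does not apply to a collar that vibrates on the neck. All participants also receive usual physiotherapy care, which may include manual therapy, exercise, drugs or invasive procedures (2.6), so another possible cause is nearly always at hand.

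Finally, the stated collection stops with treatment although participants are seen twice afterwards. The trial is meant to inform a full-scale trial of a device used at home, so its adverse event record is likely to be carried forward.

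**Working it through.** The plan gives no adverse event rate or count, so there is no figure of its own to reproduce. The check is a reading of the text plus two small calculations.

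**1. Which events are left out.** Take an event that needs medical attention and is judged unrelated.
- Serious? The medical-attention condition is met and the relatedness condition fails: no.
- Minor? It may disturb daily activities or last beyond a day, but it also fails on relatedness: no.

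The event has no category. The two relatedness conditions also differ in strength. The minor one admits a possible relation. The serious one reads as a definite relation, although a word may be missing from that sentence. On either reading relatedness is required.

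**2. Share of follow-up covered.** Calls: 4 weeks (2.9). Follow-up: 2 months from commencement (2.10), taken as 8 to 8.7 weeks.
- 4 / 8 = 50%, leaving 8 − 4 = 4 weeks.
- 4 / 8.7 = 46%, leaving 8.7 − 4 = 4.7 weeks.

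The 5-week and 2-month assessments both fall in the uncovered part.

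**3. Who knows the allocation.**

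| Role | What the article says | Adverse event task |
|---|---|---|
| Outcome assessor | Blinded (2.4) | None stated |
| Therapist | Cannot be blinded (3.2); acts as if both treatments were active (2.4) | None stated |
| Study clinician | Blinding not stated; calls weekly about adherence and fidelity (2.9) | Calls in which events are monitored |
| Judge of relatedness | Not named | Not applicable |

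The study clinician discusses use of one of two visibly different devices with each participant, so knowledge of allocation is probable. It remains an inference.

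**4. What differential attribution would do (hypothetical).** Let p be the true event rate, equal in both arms, and a the proportion called related in an arm. The recorded rate is p × a, so the ratio of recorded rates is a(iTAD) / a(iTENS) whatever p is. The arm sizes are 24 and 12 (2.5). Every value of p and a below is assumed.

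| p | a iTAD | a iTENS | Recorded iTAD | Recorded iTENS |
|---|---|---|---|---|
| 30% | 80% | 80% | 24 × 0.3 × 0.8 = 5.8 (24%) | 12 × 0.3 × 0.8 = 2.9 (24%) |
| 30% | 80% | 40% | 5.8 (24%) | 12 × 0.3 × 0.4 = 1.4 (12%) |
| 30% | 80% | 10% | 5.8 (24%) | 12 × 0.3 × 0.1 = 0.4 (3%) |
| 25% | 50% | 0% | 24 × 0.25 × 0.5 = 3 of 24 | 12 × 0.25 × 0 = 0 of 12 |

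Equal attribution leaves the recorded rates equal (first row). Unequal attribution creates a difference where none exists. The table shows the mechanism only; nothing in the article supports any particular row.

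**The case against.** The strongest reply is that much of what a reader might infer is not in the text. Four such inferences should be set aside.

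- **That an unblinded clinician judges the events.** The article calls the therapist unblinded and has the study clinician make the calls. It does not equate the two, and it names no judge of relatedness.
- **That uncertain events are never recorded.** The minor definition admits events that may be related, and no sentence tells the caller to discard other reports.
- **That a lasting neck pain flare would go unseen.** Pain intensity, pain spread and the Neck Disability Index are measured at all four time points. Global perceived effect, whose scale extends to marked worsening, is taken at the last three. A flare present at 5 weeks or 2 months would show there, without an adverse event label and without a causality judgement.
- **That a planned safety comparison is biased.** No between-arm analysis of adverse events is stated.

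Two further points have some force. The control device has wires and adhesive pads and is worn for an hour a day, so an event from wearing it can be related without any current. The article also describes the risks as minor, and the calls cover the whole treatment period.

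It can also be said that an article leaves forms and causality procedures to the full protocol. That excuses silence about who adjudicates. It does not excuse the definition, which is a printed rule, and it only partly answers the collection window, because the article names one route and dates it. The word only does not appear there, so collection at later visits is unstated rather than excluded.

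**Conclusion.** The point stands on two printed features. First, both definitions require relatedness, so an unrelated event that needs medical attention is not an adverse event in this trial. Second, the stated collection covers 46% to 50% of follow-up, taking 2 months as 8 to 8.7 weeks.

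Differential attribution between arms is a plausible risk to any count reported by arm. It rests on the assumptions that the caller knows the allocation and that the caller, or someone equally informed, decides relatedness. Its size cannot be derived from the document. Tactile acuity, the other outcomes, the sample size and the error rates are unaffected. The matter is a cheap correction worth making before data collection and not a threat to the trial's main conclusions.

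**What to change.** 1. Define an adverse event as any unwanted event during participation, regardless of cause.
2. Record it in both arms at every contact: the weekly calls, the mid-treatment visit, and the existing 5-week and 2-month visits.
3. Hold seriousness, severity and relatedness as three separate fields. State who judges relatedness and whether that person is blind to allocation, preferably blind.
4. Report all-cause events by arm, with related events as a subset.

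One practical caution: an answer about the device could unblind the outcome assessor. At the 5-week and 2-month visits the question is better put on a self-completed form that goes to someone else.

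The cost is a revised form and one question at two existing visits. No visit is added, and no sample size, error rate or clinical rule changes.
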